### Data management

Data collection will be conducted by the National Statistical Institute (INSTAT), which has extensive experience in collecting household survey data in Madagascar. We will collect data with Computer Assisted Personalized Interviews (CAPI) on Android tablets using Survey Solutions, a free software platform.

For both survey and administrative data, subject key (identifiers and subject numbers) will be kept in a secure separate location. Individual-level data collected from the census and administrative sources will be shared with the research team for the purposes of analysis with each individual having a unique respondent ID code. All documentation regarding the participants, including the consent forms and questionnaires, will be identified using appropriate participant codes. All records will be accessible only to approved survey firm personnel and research team members in password-protected files. Researchers will also make no attempts to identify any individual caregivers or children through a combination of any of the variables provided through this administrative data. In the event of a breach of confidentiality, we also consider the potential harm to subjects to be minimal as we are not collecting sensitive data.

### Statistical methods for primary and secondary outcomes

#### General analytic approach

Primary analyses will be conducted on an intention-to-treat (ITT) basis.

Identification of causal impacts will rely on the random assignment of treatment at the community level. The main impact of the program activities will be measured through a series of pair-wise comparisons of mean outcomes between the study arms. However, it is possible that by chance alone we will find a covariate imbalance between communities in different treatment arms that could confound our estimates. Therefore, we will measure theoretically significant covariates at the caregiver-child dyad level, CHW and community levels to include in a regression framework.

The potential for contamination or spillover effects for CHWs and caregiver-child dyads across communities for the program is low, as communities are self-contained and provide services to mothers and children registered in the local community.

#### Parameters of interest

Here, we describe the parameters of interest and introduce notation. Treatment, randomly assigned at the community level, is represented by two arms: group ECD sessions (T), and group ECD sessions + enhanced play materials (T +). The status quo, or control arm, is denoted by C. In notation terms, the full set of potential assignment variants is given by t = [C, T, T +] A set of individual (CHW and/or caregiver-child dyad, depending on the outcome) level covariates, X, and community-level covariates, V, will be used to adjust for imbalance that may occur by chance in the randomization process. We also include the baseline value of the outcome of interest (Y_0_) to improve precision in our models. Below, we report the parameters of interest for the primary and secondary research questions (reproduced below). Parameters that differ in outcome but not in notation by research question are combined for simplicity.*Primary Question 1: How does the integration of ECD activities into existing health and nutrition responsibilities affect the time use and task allocation of CHWs?**Secondary Question 1: How does the integration of ECD activities affect measures of CHW psychosocial wellbeing?**Primary Question 2: How does the integration of ECD activities affect participation by caregiver-child dyads in all activities led by CHWs?*

The estimands are pair-wise comparisons of each intervention arm with the control arm, for CHW or caregiver-child dyad outcomes. These comparisons are represented by the following equation:1$$\mathrm E\left[\mathrm Y\left|D=d,Y_0,X,V\rbrack-E\lbrack Y\left|C,Y_0\right.\right.,X,V\right],where\;d=\lbrack T,T+\rbrack$$*Primary Question 3: How does the availability of age-appropriate materials/activities for home-based play affect caregiver-child dyad participation in ECD activities?*

To understand how integration of toy boxes affects time/task allocation of CHWs or caregiver-child participation, we will do one pairwise comparison between the two intervention arms for this outcome. This comparison is represented by the equation below:2$$\mathrm E\lbrack\mathrm Y\vert\mathrm D=\mathrm T,{\mathrm Y}_0,\mathrm X,\mathrm V\rbrack-\mathrm E\lbrack\mathrm Y\vert\mathrm D=\mathrm T+,{\mathrm Y}_0,\mathrm X,\mathrm V\rbrack$$*Secondary Question 2: How is the treatment effect on caregiver-child dyad participation in health and nutrition activities moderated by key household and community characteristics?*

In order to estimate how the treatment effect obtained in Eq. (1) for caregiver-child dyad participation is moderated by key individual and community-level characteristics, M, we use the following estimand:3$$\left(\mathrm E\left[\mathrm Y\vert\mathrm D=\mathrm d,{\mathrm Y}_0,\mathrm X,\mathrm V,\mathrm M=1\right]-\mathrm E\left[\mathrm Y\vert\mathrm C,{\mathrm Y}_0,\mathrm X,\mathrm V,\mathrm M=1\right]\right)-(\mathrm E\left[\mathrm Y\vert\mathrm D=\mathrm d,{\mathrm Y}_0,\mathrm X,\mathrm V,\mathrm M=0\right]-\mathrm E\lbrack\mathrm Y\vert\mathrm C,{\mathrm Y}_0,\mathrm X,\mathrm V,\mathrm M=0\rbrack),\mathrm{where}\;\mathrm d=\lbrack\mathrm T,\mathrm T+\rbrack$$

#### Empirical specification

We have two primary estimating equations, which we discuss below. The first (Eq. 4) is our main specification for comparisons between each intervention arm and the control group (Primary Questions 1 & 2, Secondary Question 1). These models will be used to estimate the impact on CHW outcomes (time use and motivation) and caregiver-child dyad outcomes (participation and engagement). All specifications will control for the method of randomization by including strata indicator variables, month fixed effects to account for time-varying unobservable (to the researcher) factors, and correcting standard errors for clustering at the community level. For clarity, we reproduce one set of equations here, but they can be applied to either CHW-level or caregiver-child dyad-level analysis.

Let the outcomes of interest will be represented by $${Y}_{ijt}$$, where the subscript refers to CHW (or caregiver-child dyad) *i*, in community *j*, at time *t*.

The main ITT impact of each intervention arm on the outcome of interest is estimated as follows:4$${Y}_{ijt} = \alpha + {\beta }_{1}{T}_{j} +{\beta }_{2} {{T}_{+}}_{j}+ \gamma {Y}_{ij0} + {\delta }_{1}{X}_{ijt}+ {\delta }_{2}{V}_{jt}+ {\theta }_{s}+ {\lambda }_{t} + {\varepsilon }_{ijt}$$

where $${T}_{j}$$ or $${{T}_{+}}_{j}$$ are indicators for the random assignment of community j to treatment, $${Y}_{ij0}$$ are baseline outcomes for CHW (or caregiver-child dyad) i (ANCOVA specification), $${X}_{ijt}$$ are CHW-level (or caregiver-child level) covariates (e.g. age, gender, education level), are $${V}_{jt}$$ are time-varying community-level characteristics (e.g. shocks, prices/wages), $${\theta }_{s}$$ are strata fixed effects (randomization triplet fixed effects), $${\lambda }_{t}$$ is a set of month fixed-effects, and $${\varepsilon }_{ijt}$$ are error terms clustered at the community level.

β_1_ and β_2_ represent the average impact of being assigned to T or T + over 12- and 6-month periods, respectively, relative to the control group. Testing primary question 1 and primary question 2 is equivalent to testing whether (H0: β_1_ = 0 and (H0: β_2_ = 0).

To address Primary Question 3, we restrict the sample to the communities that are offered any ECD intervention (T or T +) and estimate the following equation:5$${Y}_{ijt} = \alpha + {\beta }_{2} {{T}_{+}}_{j}+ \gamma {Y}_{ij0} + {\delta }_{1}{X}_{ijt}+ {\delta }_{2}{V}_{jt}+ {\theta }_{s}+ {\lambda }_{t}+ {\varepsilon }_{ijt}$$

These analyses will occur in a restricted sample of only communities where T = 1 or T + = 1. Here, testing (H0: β_2_ = 0) allows to test whether being assigned T + provides any additional benefit over and above T.

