##### Transitions across age groups

The study period will cover two cycles of the 12 ECD group sessions. After six months, participants of the first three age groups will be offered to “graduate” to the next age group’s curriculum, and new participants will be added to the youngest age group. At this time, if there are participants who decide not to move to the subsequent age group cycle at the transition point, wait list participants will be randomly offered a spot in the age group.

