##### Treatment Plus (T +): Status quo health and nutrition program + fortnightly group ECD sessions, based on Reach Up and Learn curriculum and behavioral supportive nudges + individual toy boxes with age-appropriate toys for home-based play

After six months of program operation, half of the ECD communities will be randomly allocated to receive an enhanced play materials and activities package for home use to complement the Reach Up and Learn curriculum (T +) (Fig. 2). To promote sustained play between group sessions and daily practice, participating families will receive age-appropriate toy/books boxes at the start of the 6-month cycle. This toy box is composed of one developmentally-appropriate toy given as a gift to the caregiver-child dyad and kept at home. In addition, caregiver-child dyads will be able to borrow a toy and a book from the ECD group session play activities every two weeks to increase play variety and to practice activities learned with the CHWs. Caregivers will learn how to use the toys to play with their children, with lessons at each meeting providing scaffolding to encourage developmental growth. The 6-month delay in implementing T + increases the power to detect CHW time cost differences from integrating ECD group activities (T) with the health and nutrition program, while maintaining sufficient power to detect differences in take up related to the enhanced play materials (T +) by the caregivers (see section Power Calculations).

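### Eq. 4 and Eq. 5 use arm indicators that stay constant over time although T+ starts only after month 6; run as written, Eq. 5 recovers about half of a constant toy-box effect

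*Protocol article*

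**What the plan says.** The Treatment Plus (T +) section sets a staggered start: "After six months of program operation, half of the ECD communities will be randomly allocated to receive an enhanced play materials and activities package". The section Transitions across age groups adds that "The study period will cover two cycles of the 12 ECD group sessions", each lasting six months. So in months 1–6 all 50 ECD communities deliver T, and only in months 7–12 do T and T+ differ. The Treatment Plus section gives the reason for the delay: it "increases the power to detect CHW time cost differences from integrating ECD group activities".

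Under Empirical specification, Eq. 4 regresses the monthly outcome on T_j and T+_j, which "are indicators for the random assignment of community j to treatment". These terms carry only the community subscript, whereas the covariates X_ijt and V_jt also carry a time subscript. Eq. 5, for Primary Question 3, keeps T+_j and limits the sample to T and T+ communities; no limit on months is stated. The same section describes β1 and β2 as the mean effects of T and T+ assignment "over 12- and 6-month periods, respectively, relative to the control group".

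**The concern.** Two statements in one section do not fit together. With indicators fixed over time, a T+ community counts as T+ from launch, and both coefficients are averages over whatever months enter the regression. Neither equation can then give a 12-month average for T and a 6-month average for T+.

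Three things are at stake. For Primary Question 3, the T+ versus T contrast would include six months in which the two arms receive the same thing, which pulls the estimate toward no benefit of play materials. For Primary Questions 1 and 2, β2 would not be the T+ effect that the text describes. And the months in which T+ communities deliver T alone would not contribute to the T coefficient, although that is the stated purpose of the delay.

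**Working it through.** **Inputs.** From the article: T+ starts after month 6 of 12; 25 communities per arm; two CHWs per community; for CHW time, one baseline and 11 follow-up measurements, autocorrelation ρ of 0.5 or 0.7, ICC of 0.2 or 0.3, 80% power for 0.5 SD; for dyads, detectable effects of 0.31 SD (ICC 0.1) and 0.47 SD (ICC 0.3) with 25 treatment and 25 control communities. Assumed, because not stated: two-sided α of 0.05, and that the dyad figures refer to 80% power.

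**1. The plan's own figure.** For r follow-ups, let f(r, ρ) = [1 + (r − 1)ρ]/r − ρ². Then n per arm = 2(1.960 + 0.842)² × f/0.5², multiplied by 1 + ICC. With r = 11 and ρ = 0.5, f = 6/11 − 0.25 = 0.2955 and n = 18.55. The three ICCs give 18.55, 22.26 and 24.12, rounded up to 19, 23 and 25. With ρ = 0.7 the results are 14.90, 17.88 and 19.37, rounded up to 15, 18 and 20. All six cells of Table 1 reproduce. The formula counts CHWs, while the table is labelled in clusters, so 25 clusters of two are more than the formula asks for.

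**2. Eq. 5 as written.** Let δ be a constant toy-box effect from the switch onward.
- 12 monthly observations: (6 × 0 + 6 × δ)/12 = 0.50δ.
- 11 post-launch observations: 5/11 = 0.45 to 6/11 = 0.55 of δ.

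**3. Power for Primary Question 3.** Carry the dyad figures over to T versus T+ and hold the standard error at that implied by 80% power.
- ICC 0.1: SE = 0.31/2.802 = 0.111; the expected coefficient is 0.155.
- ICC 0.3: SE = 0.47/2.802 = 0.168; the expected coefficient is 0.235.
- Either way, power = Φ(0.5 × 2.802 − 1.960) = Φ(−0.559) = 29% (25% to 33% with 11 months). An 80% chance would need a true effect of 0.62 or 0.94 SD.

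The article also applies the T versus T+ contrast to CHW time, where its own inputs give a second illustration without holding the SE fixed. With ρ = 0.5 and ICC 0.3, SE = √[f × (1.3/2) × 2/25], which is 0.1232 over 12 months (f = 0.2917) and 0.1317 over months 7–12 (f = 0.3333). For a toy-box effect of 0.5 SD, power is Φ(0.25/0.1232 − 1.960) = 53% on all months and Φ(0.5/0.1317 − 1.960) = 97% on months 7–12.

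**4. Eq. 4 as written.** If the ECD effect is constant, β2 = ECD effect + δ/2, and only β2 − β1 is halved.

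**5. Power for T.** With fixed indicators, β1 compares 25 T with 25 control communities whether or not T+ is delayed. In months 1–6 alone, using all ECD communities would give 50 against 25: SE = √[0.3333 × 0.65 × (1/25 + 1/50)] = 0.1140. The detectable effect (2.802 × SE) is then 0.319 SD, against 2.802 × 0.1232 = 0.345 SD for 25 against 25 over 12 months. Power for 0.5 SD in the latter case is already Φ(0.5/0.1232 − 1.960) = 98%.

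**6. Simulation check.** 600 runs with 75 communities, two CHWs each, 12 months, ρ = 0.5, ICC 0.3, an ECD effect of 0.50 SD and a toy-box effect of 0.40 SD from month 7:

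| Coefficient | Mean | SE |
|---|---|---|
| Eq. 4 as written, β1 | 0.505 | 0.120 |
| Eq. 4 as written, β2 | 0.698 | 0.116 |
| Eq. 5, all 12 months | 0.193 | 0.125 |
| Eq. 5, months 7–12 | 0.393 | 0.134 |
| Time-varying coding, T | 0.503 | 0.106 |
| Time-varying coding, T+ | 0.897 | 0.129 |

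The true T+ versus control effect in months 7–12 is 0.90. Fixed coding gives about 0.70 = 0.50 + 0.40/2; time-varying coding recovers it. The SE for T falls from 0.120 to 0.106, or 12%.

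**The case against.** The sentence interpreting the coefficients gives T+ a 6-month period, so the authors probably mean T+ to count only from the switch. If T+ communities are coded as T until then, that sentence fits, nothing is diluted and the power gain is obtained. The article also says that one set of equations stands for several analyses, and exact exposure coding may sit in an analysis plan that is not shown.

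Much of this stands. A reader might infer that the trial will certainly average T+ over all 12 months; the documents do not say so. The dilution is what follows if the equations are run literally. But this is more than omitted detail: the equations are printed with subscripts, other terms do carry a time subscript, and the sample restriction for Eq. 5 is stated twice, by community only. Following them gives the wrong estimate.

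Two further limits are fair. The dyad detectable effects are stated for treatment versus control in the health and nutrition programme, not for T versus T+ in ECD attendance, so the 29% is an extrapolation. And the article puts no figure on the gain from the delay, so the loss cannot be measured against a promise.

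**Conclusion.** The point holds as a contradiction between the equations and the text, and it matters mainly for Primary Question 3. Run as written, Eq. 5 estimates about half of a constant toy-box effect (45% to 55% with 11 post-launch months). Power of about 29% at the stated detectable effects assumes that these are 80%-power figures, that they carry over to T versus T+, and that the standard error is the same, which requires stable community effects over the year.

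Two stronger readings are not supported. T+ versus control in Eq. 4 is not halved: β2 is the ECD effect plus about half the toy-box effect, so it is mislabelled rather than cut in two. Nor is the comparison of T with control on CHW time put at risk: the missed gain is about 12% of the standard error, and power for 0.5 SD is already about 98% at ρ = 0.5 and ICC 0.3.

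**What to change.** - Give treatment a time subscript in Eq. 4. Code T+ communities as T until the switch and as T+ afterwards. An equivalent form uses ECD_jt = 1 in T and T+ communities from launch and TOY_jt = 1 in T+ communities from month 7; T+ versus control is then the sum of the two coefficients.
- State that Eq. 5 uses months 7–12 only.
- Reword the sentence on β1 and β2 so that the periods match this coding.

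No new data are needed. Limiting Eq. 5 to six months raises its SE a little (0.125 to 0.134 in the simulation) while the expected coefficient doubles.

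One small downside: the pooled ECD coefficient gives more weight to months 1–6. With variances proportional to 1/50 + 1/25 = 0.06 in months 1–6 and 1/25 + 1/25 = 0.08 in months 7–12, the weights are 4:3, or 57% and 43%. If the ECD effect differs between cycles, the pooled figure favours the first, and the T+ coefficient in Eq. 4 absorbs part of the difference. Report the ECD effect by cycle as well.

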#### Subgroup analyses

For Secondary Question 2, subgroup analysis will be carried out by documenting the differential impact of the two interventions along key household and community-level characteristics. We will estimate heterogeneity on the pooled treatment arms interacting the characteristic of interest with the treatment variable, as well as explore the use of recent developments in machine learning methods [30].

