### Sampling, stratification and randomization

In order to capture efficiency gains from adjusting from observable differences in the design of the randomized experiment, we conducted stratified sampling [28]. We partitioned the covariate space into 16 strata, with stratification criteria that included region (Amoron’i Mania and Haute Matsiatra), remoteness of the community (above/below the median Euclidean distance to the closest health center), population size of the catchment area (above/below median number of children in the 6–30 months old age range), and CHW education level (above/below secondary level of educational attainment).

Within each of the 16 strata, we sampled six or 12 communities (one sextuplet drawn from each of seven smaller strata and two sextuplets drawn from each of nine large strata) to create a set of 25 sextuplets that are comparable along the stratification dimensions. Next, we randomly drew three communities selected from each sextuplet and allocated each to one of three possible arms (i.e. allocation ration of 1:1:1 in two treatment arms and one control arm) for a total of 75 communities in the final sample. This sampling approach ensures that each community has a cluster of comparable communities within its assigned stratum and allows for up to three back up communities for the potential need for replacement in case of refusal or drop-out by participating communities [28, 29]. All sampling and randomization were done by key research personnel using standard and reproducible computer-assisted software packages in Stata 16.

The random generation sequence and the random assignment of (i) communities to treatment arms and of (ii) households in case of over-subscription in T and T + will be performed by the research team. Due to the nature of the interventions, it is impossible to blind participants to their intervention group assignment. Interviewers will not be blinded as they will ask participants about their program-related experiences. However, the data will be masked to group assignment during the data analysis phase to blind the data analysts.

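### Secondary Question 2 defines moderation separately for T v C and T+ v C (Eq. 3), but the planned subgroup analysis fits one pooled interaction, which estimates the average of the two

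*Protocol article*

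**What the plan says.** In the protocol article, Parameters of interest sets out the base effects: "The estimands are pair-wise comparisons of each intervention arm with the control arm, for CHW or caregiver-child dyad outcomes". Eq. 3 then builds on them. It is introduced as the way to estimate "how the treatment effect obtained in Eq. (1) for caregiver-child dyad participation is moderated by key individual and community-level characteristics", and it is written for d = T and d = T+, each against C. Secondary Question 2 therefore has two parameters.

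Subgroup analyses opens with the same plural aim, "documenting the differential impact of the two interventions along key household and community-level characteristics". The next sentence gives the estimator: "We will estimate heterogeneity on the pooled treatment arms interacting the characteristic of interest with the treatment variable". That is one treatment variable and one interaction per characteristic. The same sentence mentions machine-learning methods, but only as something to explore.

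No other equation supplies arm-specific interactions. Eq. 4 and Eq. 5 contain no interaction term, and Eq. 4 is assigned to Primary Questions 1 and 2 and Secondary Question 1. The main model does keep the arms apart: its two coefficients "represent the average impact of being assigned to T or T + over 12- and 6-month periods, respectively, relative to the control group".

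**The concern.** The estimand and the estimator are both stated, and they do not match. Eq. 3 implies two null hypotheses: no moderation of the T effect, and no moderation of the T+ effect. The pooled interaction tests a third, that the average of the two is zero.

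The stake is attribution. The section on post-trial care says that results will feed back into the redesign of the integrated package, and T and T+ are different candidates for that package. A significant pooled interaction could be read as applying to both packages when only one is moderated. A null result could hide moderation in one of them. As written, neither Eq. 3 parameter would be reported.

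**Working it through.** The documents give no sample size, power or effect size for moderation, so there is no figure of the plan to reproduce. The check has two parts.

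**1. What the pooled coefficient estimates**

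Inputs from the protocol:
- Allocation is "allocation ration of 1:1:1 in two treatment arms and one control arm", with 25 communities per arm.
- The T+ component comes late: "After six months of program operation, half of the ECD communities will be randomly allocated to receive an enhanced play materials and activities package". T and T+ communities therefore receive the same programme in months 1-6.

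Write m_T and m_T+ for the two Eq. 3 parameters. With equal arm sizes, and the moderator M similarly distributed across arms, the pooled interaction is

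pooled = (m_T + m_T+) / 2.

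This was confirmed by noise-free least squares on a balanced layout (three arms, binary M, 12 months, T+ equal to T in months 1-6). The moderation values are assumed.

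| Assumed moderation in months 7-12 (T, T+) | Pooled, months 7-12 | Pooled, all 12 months |
|---|---|---|
| 0.3, -0.3 | 0.00 | 0.15 |
| 0.3, 0 | 0.15 | 0.225 |
| 0, 0.3 | 0.15 | 0.075 |
| 0.2, 0.2 | 0.20 | 0.20 |

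Separate T x M and T+ x M terms recover both parameters exactly in months 7-12 in every row. Over 12 months the T+ coefficient is itself a mixture, because half of its months are plain T. In the second row, for example, it is (0.3 + 0)/2 = 0.15.

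**2. What this does to power**

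Assumptions: 25 triplets; a within-community contrast (M = 1 minus M = 0) with SD 1; a two-sided 5% t test on 24 df; equal weight per month; the same SD for a 6-month or a 12-month average.

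- SE of one arm v control: sqrt(2/25) = 0.283.
- SE of pooled arms v control: sqrt(1.5/25) = 0.245.
- Ratio: 0.245/0.283 = 0.866. The arm-specific SE is thus 1/0.866 = 1.15 times the pooled SE.
- A moderation of 0.826 SD gives noncentrality 0.826/0.283 = 2.92, which is 80% power for one arm.

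| Scenario | Pooled moderation | Noncentrality (÷ 0.245) | Pooled power |
|---|---|---|---|
| Months 7-12, one arm only moderated | 0.826/2 = 0.413 | 1.69 | 37% |
| Months 7-12, opposite signs | 0 | 0 | 5% |
| 12 months, T's moderation vanishes in T+ after month 6 | 0.826 x (1 + 0.5)/2 = 0.620 | 2.53 | 68% |
| 12 months, T's moderation reverses in T+ after month 6 | 0.826 x (1 + 0)/2 = 0.413 | 1.69 | 37% |
| Equal moderation in both arms | 0.826 | 3.37 | 90% |

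One further 12-month case: if moderation comes only from the toy boxes, the T+ average is 0.413. Pooled power is then 13% (0.207/0.245 = 0.84), against 29% for the arm-specific test (0.413/0.283 = 1.46). Both are weak, because six of the T+ months carry no signal.

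**The case against.** **Pooling is defensible.** Secondary Question 2 speaks of the treatment effect in the singular, and ECD integration is common to both arms. For the first six months the arms are the same programme, so pooling is right for that half and gains precision. With 25 communities per arm and main-effect detectable differences already at 0.31 to 0.47 SD, pooling for a heterogeneity analysis is reasonable. All of this stands as a case for reporting a pooled estimate. It does not make that estimate the quantity in Eq. 3, and the protocol neither defines a pooled estimand nor states that moderation is equal across arms.

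**Pooled may mean the combined sample.** A reader might take the sentence to mean all arms in one model with separate interactions. The singular treatment variable does not support that.

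Four stronger readings are tempting, and the documents do not support them:

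- *That the pooled test can never estimate Eq. 3.* It does so when moderation is equal in both arms.
- *That it loses 43 points of power (80% to 37%), or has only 5% power under opposite signs.* Those figures need an analysis of months 7-12 alone. Subgroup analyses states no window. Over 12 months the loss is about 12 points in the vanishing case, and power is about 37% in the reversing case.
- *That rejecting in 37% of trials when one arm is unmoderated is an inflated Type I error.* The pooled null is false in that scenario, so rejection is correct. The error would lie in assigning the result to the unmoderated arm.
- *That the protocol's own theory predicts arm-specific moderation.* Its argument about play materials at home concerns attendance at ECD sessions. Secondary Question 2 concerns health and nutrition participation, for which no such theory is given, and nothing in the documents suggests opposite signs.

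**The power model does not cover community moderators.** Remoteness is constant within a community, so the within-community contrast does not exist for it. The averaging result still applies, but the power figures do not.

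**Conclusion.** The mismatch is real and lies between two statements in the current text. Eq. 3 asks for two moderation parameters, and Subgroup analyses estimates their average. Because T and T+ coincide in months 1-6, the two can diverge only through months 7-12, so the size of the problem depends on the window analysed.

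Under the assumed effects, pooled power ranges from about 37% to 68% across the one-arm (months 7-12), reversing and vanishing (12 months) scenarios, against 80% for an arm-specific test of T. It rises to about 90% when moderation is equal. These figures illustrate rather than predict: the documents give no moderation effects, and the figures rest on the assumptions listed with the calculation. The averaging result does not depend on the effect sizes. It needs only equal arm sizes and a similar distribution of M across arms.

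No primary test is affected. This is a secondary question, worth correcting because the correction is cheap and the results are meant to inform package design.

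**What to change.** In Subgroup analyses, replace the single pooled interaction with M, T x M and T+ x M in the Eq. 4 framework. Estimate the T+ interaction for months 7-12, in line with the 6-month definition of the T+ coefficient under Empirical specification, and state the window for the T interaction. Report both coefficients with confidence intervals and a test of their equality; for that test, take both over months 7-12. Keep the pooled interaction as a stated linear combination, labelled average ECD moderation, for its precision.

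If the sponsor wants only the pooled quantity, the alternative is to redefine Eq. 3 as any ECD against C and state the period. The protocol would then no longer promise results for the two interventions separately.

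The cost is a sentence or two of wording and one extra interaction term per moderator, with no new data. Over the same months, arm-specific SEs are about 15% larger than the pooled SE. Using only months 7-12 for T+ may widen its interval further, by an amount that depends on the correlation between months, which the protocol does not give for dyad participation. There are also more estimates to report.
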